## Trial outcome measures

### Primary endpoint

Cumulative time with clinically detected epileptogenic seizure activity over 36 hours.

### Secondary endpoints

Feasibility will be assessed by ability to implement/operationalise the BCV for use on the high dependency ward in Kilifi County Hospital (assessed by whether this can generate negative pressure ventilation as per specification by the Hayek recommendations and averts respiratory safety endpoints).

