### General objectives

We aim to conduct a Phase I trial to demonstrate the feasibility and safety of non-invasive ventilatory support in cerebral malaria (Blantyre coma scale ≤2) and history of seizures to generate preliminary data on seizure control and neurological status in those surviving to 28 and 180 days.

**
*Specific objectives*
**

**(i)** To initially examine whether it is safe, feasible and practical to implement a protocol for the use of NIV with BCV, with or without the use of Hi-Flow AirVO2 technology (to treat hypercarbia (PCO
_2_))
**(ii)** To implement our refined-protocol for BCV use in cerebral malaria in addition to prophylactic ASM (LVT) to reduce the complications of cerebral malaria.
**(iii)** To estimate the occurrence of adverse events using BCV, including episodes of bradypnoea or apnoea; hypoxaemia (oxygen saturations <92%); number of episodes of hypercarbia (pCo2>45mmHg since this will worse brain swelling), and number of aspiration events (given that all children will routinely having nasogastric tubes and regular suction)

**Site:** High dependency ward in Kilifi County Hospital, Kenya.

**Study design**: Phase I trial to generate feasibility, safety and preliminary data on seizure control and survival to 28 days of non-invasive ventilatory support and seizure prophylaxis in cerebral malaria.

**Study Population:** 30 children hospitalised with cerebral malaria

**
*Inclusion criteria*
**

1. Aged 3 months and 12 years (up to 40 kg in weight for paediatric dosing of LVT) admitted to the paediatric ward.2. Current or recent evidence of
*P. falciparum* malaria (slide or rapid diagnostic test (RDT) positive)3. Blantyre Coma Score2 or less that persists even after correction for concurrent hypoglycaemia (defined as glucose <3 mmol)4. History of seizures in this illness5. Guardian or parent willing and able to provide consent

**
*Exclusion criteria*
**

1. Known cerebral palsy or significant neuro-development delay (which will affect endpoint assessment)2. Skin disease or burns preventing use of the BCV3. Respiratory or cardio-respiratory arrest prior to enrolment4. A comorbidity which clinician believes has a significant risk of poor outcome e.g. malignancy, end-stage renal failure, major cardiac condition

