### Sample size determination

This is a Phase I trial designed to test the feasibility, tolerability and safety of using non-invasive ventilatory support in cerebral malaria. We plan to initially enrol 10 children with CM and a history of seizures (see inclusion criteria above) as this selects a high-risk group with ~90% risk of further seizures who will all require first line (diazepam) and many will require second-line (phenobarbitone) anticonvulsants, all with an inherent risk of respiratory depression or aspiration (15% in the control group of the Malawi trial Trials.gov (Trial reference NCT01982812)).

Following this initial phase the next 10 children will receive a neuroprotective strategy of BCV plus LVT 40 mg/kg loading dose and 30mg/kg every 12 hours given via nasogastric tube for 3 days or until coma resolution.

If this reduces seizures that are short lived and are not clinically-relevant (so 80% do not require additional ASM (based on the judgement of an independent Data Monitoring Committee, i.e. that do not require addition ASMs with minimal adverse events), then an additional 10 children will be studied using LVT at this dosage, without dose escalation.

If this fails to adequately control seizures, the neuroprotective strategy of BCV plus a higher dose (150%) of LVT will be studied, namely 60 mg/kg loading dose and 45mg/kg every 12 hours given via nasogastric tube for 3 days or until coma resolution.

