### Trial treatments

We will study 30 children. This will be done sequentially (10 children with usual care + BCV; then 10 children with BCV given 40 mg/kg loading dose of LVT and 30mg/kg every 12 hours; and the final 10 children (with or without BCV) will receive LVT but the dose will depend on whether adequate seizure control (see above) has been achieved in the previous 10 children as follows. Firstly, if seizure control is adequate then an additional 10 children will be studied with BCV plus LVT at the same dosage or secondly, if seizure control is not adequate then LVT at a higher dose will be given 60 mg/kg loading dose and 45mg/kg every 12 hours.

The first 10 children in the study will have the usual care for cerebral malaria with the addition of BCV. This will allow us to assess feasibility and tolerability and to provide initial refinements for its use. The BCV ventilation intervention period
**will be from study enrolment** until when a child can respond to stimuli (Blantyre coma scale 3 or more) sustained over a period of 4 hours.

Feasibility will be judged by the ability of BCV to safely institute negative pressure ventilation, and to support respiration during periods of hypoventilation or apnoea. In addition, we will assess whether children are able to tolerate the use of BCV (judged by children remaining comfortable during transition from coma to a semiconscious state) and whether we are able to clear any secretions by regular suctioning (if this is judged to be a problem). Additional practical considerations will be considered such as whether BCV interferes with monitoring the child and time required by the nursing staff to implement and maintain its use.

This will then be followed by a second phase where we will implement a neuroprotective strategy or treatment bundle: where prophylactic ASM will be used in combination immediately following feasibility studies of use of BCV to provide negative pressure ventilation (NPV) +/- AIRVO2 High Flow (children with BCS≤2). We will use LVT at an initial loading dose of 40 mg/kg followed by 30mg/kg every 12 hours. This will be given via nasogastric tube for 3 days or until coma resolution.

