### Safety endpoints

Aspiration (sudden decrease in oxygen saturations, and/or denovo presence of coarse chest crepitations, with evidence of gastric reflux/aspirate in the oropharynx).

Episodes of hypercarbia (defined as pCO2 level of greater than 45 mmHg).

Episodes of bradypnoea and hypoxaemia (oxygen saturation <92%) in a child with unrousable coma (Blantyre coma scale≤2) (bradypnoea defined as <10, 15 or 20 breaths/minute over 3 minutes for those aged <6m, 6–36m and >36m respectively).

Development of hypotension (defined as systolic blood pressure <50 mm Hg in children younger than 12 months; <60 mm Hg in children 1–5 years and <70 mm Hg in children olderthan 5 years of age). Use of additional ASMs. Neurological sequelae at day 180, Day 28 and day 180 mortality. Re-admission to hospital through day 180. Serious adverse events through day 180. Grade 3/4 adverse events through day 180. Length of initial hospitalisation. De-novo evidence of neurological impairments will be ascertained using a modified Kilifi Developmental Index
^
45
^ (which we have adapted to use for the COAST trial)
^
46
^.

Serious adverse events (SAEs) will use the standardized definitions. SAEs will be independently reviewed in real-time by the DMC. Adverse events will be graded following the Common Toxicity Criteria v5.0:

(
https://ctep.cancer.gov/protocoldevelopment/electronic_applications/docs/CTCAE_v5_Quick_Refe rence_5x7.pdf).

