The clinically important adverse events potentially related to the intervention for a Bayesian monitoring approach to be considered by the DMC in this Phase I trial will be an aspiration or respiration depression event (defined as a sudden decrease in oxygen saturations, and/or de-novo coarse chest crepitations, with evidence of gastric reflux/aspirate in the oropharynx). As the Phase II trial comparing levetiracetam to standard of care (control arm) in Malawi had not been reported when this protocol was designed we used the data posted on Trials.gov for the to inform the anticipated event rates. This reported that there were 3/21 events (15%) in the control arm (Trials.gov: NCT01982812). Thus, this has informed a beta prior distribution of (0.23, 1.32) with mean 0.15 (i.e. 15% children experiencing an event) and variance 0.05. We have defined a stopping threshold of 20%, as a previous case series identified very few aspiration events (<1%) in children with acute respiratory failure using the BCV machine
^
35
^. The posterior probability τ was empirically set at 0.95 for the evaluation of this rule
^
47
^. Thus, according to the derived Bayesian decision rule, enrolment will be stopped if the posterior probability of the number of clinically important adverse events being above the target threshold (20%) is higher than 0.95.

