### Clinical management

Members of the clinical team and study team will all receive pre- and peri-trial training on the management of severe malaria and the use of BCV. A manual of operations for the trial will be available for the study team, to anticipate and troubleshoot any potential issues. This is the approach that was taken for training of AirVo2 in the COAST trial and this ensured adherence to the protocol
^
46
^. Our programme has a dedicated high dependency ward with a long track record of research and care for children with cerebral malaria and has the relevant expertise in the management of this condition. The usual protocol for management of seizures will be followed.

One potential risk of BCV use is aspiration; however this risk is minimal (<1%)
^
35
^, and further all children with coma routinely have nasogastric tubes placed (to drain gastric contents and secretions) and regular suction (oropharynx) which would apply to all children enrolled in this study as this is part of usual practice. The other potential risk is retention of carbon dioxide, which will be explored in detail in this Phase I study, using non-invasive end-tidal capnography (E’CO2) monitoring. High measures of E’CO2 will be verified by venous blood gas measurement (PCO2). If indicated (PCO
_2_ >45 mmHg) then AIRVO2 will be started to wash out CO
_2_ since hypercarbia can worse brain swelling. Continuous capnography is increasingly being used across Africa and supported by the Safe Surgery initiative
^
48
^, as it provides information on the efficiency of respiratory cycle (in non-intubated as well as intubated patients) which is an important parameter to capture in children with cerebral malaria as well as providing a continuous reading of expired CO2. As transcutaneous monitoring is not possible (or affordable in the long-term) our group (and external expert collaborators) prefer use of capnography by regular sampling expired gas from nasal cannulae. All abnormal measurements will be checked against a venous blood gases (0.2mls blood) as an alternative method of measurement. Finally, bag and mask ventilation is also available for children developing short term apnoea who are not ‘rescued’ by BCV.

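### The Bayesian safety rule is named for aspiration or respiratory depression but counts only events with reflux, and the respiratory endpoints behind the feasibility measure omit apnoea

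*Protocol article*

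**What the plan says.** All references are to the protocol article.

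- **General objectives, specific objective (iii)** sets out to estimate "adverse events using BCV, including episodes of bradypnoea or apnoea", with hypoxaemia as a separate item, followed by hypercarbia and aspiration.
- **Trial treatments** judges feasibility by BCV's ability to deliver negative pressure ventilation safely and "to support respiration during periods of hypoventilation or apnoea".
- **Secondary endpoints** expresses feasibility as whether BCV can "generate negative pressure ventilation as per specification by the Hayek recommendations and averts respiratory safety endpoints".
- **Safety endpoints** lists aspiration (with reflux or aspirate), hypercarbia (pCO2 above 45 mmHg), and "Episodes of bradypnoea and hypoxaemia (oxygen saturation <92%) in a child with unrousable coma", with "bradypnoea defined as <10, 15 or 20 breaths/minute over 3 minutes" by age band. Apnoea does not appear. Serious adverse events and grade 3/4 events are also listed, and the DMC reviews serious events in real time.
- **Interim reviews** names the monitoring event as aspiration or respiratory depression and gives it one definition: "sudden decrease in oxygen saturations, and/or de-novo coarse chest crepitations, with evidence of gastric reflux/aspirate in the oropharynx". The prior is Beta(0.23, 1.32). The rule acts when the posterior probability of a rate above 20% exceeds 0.95.
- **Sample size determination** describes the anticonvulsants in use as "all with an inherent risk of respiratory depression or aspiration (15% in the control group" of the Malawi trial).
- **Clinical management** states that "bag and mask ventilation is also available for children developing short term apnoea who are not" rescued by BCV.

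**The concern.** The study hypothesis is that negative pressure ventilation prevents respiratory arrest. A child who stops breathing on BCV and has to be bagged is direct evidence about that hypothesis, and the article anticipates such children. Yet neither formal measure is built to count them. The stopping rule counts them only if there is also evidence of reflux. The listed respiratory endpoints count them only through a consequence: raised CO2, desaturation, or a low rate over three minutes.

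Two things are at stake. First, the stopping rule miscounts the event it is named for, and its prior describes a wider event than the one it tallies. Any shortfall favours continuing. Second, a summary of feasibility built only on the listed respiratory endpoints could look better than the bedside experience.

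**Working it through.** **1. Setting the definitions side by side.**

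| Place | Apnoea | Bradypnoea and hypoxaemia | Respiratory depression without reflux |
|---|---|---|---|
| Objective (iii) | named | listed separately | covered by bradypnoea or apnoea |
| Trial treatments | named | hypoventilation named | covered |
| Safety endpoints (used by Secondary endpoints) | not named | joined by *and* | only via pCO2, saturation or the 3-minute rate |
| Monitoring event, Interim reviews | not named | not used | in the event's name, excluded by its definition |
| The 15% figure, Sample size determination | not named | not used | included in its description |

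**2. The prior reproduces.** Mean = 0.23/(0.23 + 1.32) = 0.148. Variance = 0.23 × 1.32/(1.55² × 2.55) = 0.0496. The article gives 0.15 and 0.05.

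**3. The rule.** With k events in n children the posterior is Beta(0.23 + k, 1.32 + n − k). Pr(rate > 0.20) is:

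- n = 10: 0.704 at k = 3, 0.889 at k = 4, 0.970 at k = 5
- n = 20: 0.920 at k = 7, 0.970 at k = 8
- n = 30: 0.943 at k = 10, 0.976 at k = 11

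So the rule prompts at 5/10, 8/20 and 11/30. As an example of the mechanism, take 3 aspirations and 2 bagged apnoeas without reflux among the first 10 children. The rule as defined scores 3/10 (0.704, no prompt). Counting both kinds gives 5/10 (0.970, prompt). The example is chosen to straddle the boundary and says nothing about how often this would happen.

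**4. Chance of a prompt within 30 children.** This is the exact probability of crossing 0.95 at any look, checking after every child and pooling all 30. By true rate of the counted event:

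| True rate | 10% | 15% | 20% | 24% | 27% | 30% | 40% |
|---|---|---|---|---|---|---|---|
| Prompt | 1.6% | 5.4% | 14.4% | 26.4% | 37.9% | 50.4% | 85.2% |

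Counted rate = combined rate × (1 − share without reflux). The article gives neither quantity, so both are assumed. At a combined rate of 30%:

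- share 10%: 0.30 × 0.9 = 27%, prompt 37.9%
- share 20%: 0.30 × 0.8 = 24%, prompt 26.4%
- share 50%: 0.30 × 0.5 = 15%, prompt 5.4%
- both kinds counted: 30%, prompt 50.4%

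**5. Can the bradypnoea item catch an apnoea?** Take the thresholds as printed and read the 3 minutes as a mean rate. A pause of t minutes then meets the rate criterion if t > 3 × (1 − threshold/background rate). Background rates are assumed.

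- Under 6 months (threshold 10; 30, 40, 50/min): 2.0, 2.25, 2.4 minutes
- 6–36 months (threshold 15; 25, 30, 40/min): 1.2, 1.5, 1.9 minutes
- Over 36 months (threshold 20; 25, 30, 40/min): 0.6, 1.0, 1.5 minutes

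If the rate must stay low throughout, the pause must last 3 minutes at every age. Read literally, the item also needs saturation below 92%. A pause ended promptly by bagging would often fall short in the younger children, and less reliably so in those over 36 months.

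**The case against.** The strongest reply is that apnoea is less hidden than the definitions suggest. Much of it stands.

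- A reader might infer that an apnoea registers only if saturation falls. The article does not support that. Hypercarbia is a separate endpoint, Clinical management provides continuous capnography with venous confirmation, and step 5 shows that a fairly short pause in an older child can meet the bradypnoea rate.
- A reader might infer that feasibility ignores apnoea. It does not: the Trial treatments criterion is current text and names it. Objective (iii) commits to estimating apnoea, though not to judging BCV on it. What is left is a mismatch between that criterion and the endpoint meant to express it.
- A reader might infer that the DMC would not see these events. Serious adverse events reach it in real time, and the Bayesian rule is described as prompting it to consider stopping. The gap is in the formal count.
- A reader might quote 5.4% against 50.4% as the size of the error. That contrast depends on an unsourced 50% share; at 20% it is 26.4% against 50.4%.
- Hypoventilation and respiratory arrest are the disease's own agonal events, and the 20% threshold is justified by the low aspiration rate reported with BCV. Widening the event without revisiting the threshold would charge some disease events to the intervention. This is a fair limit on the fix.
- A manual of operations and case record form exist but are not shown, and may record bagging or define a pause. That would ease data capture, but it would not alter the printed event definition.

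None of this answers the central point. The monitoring event names respiratory depression and then defines it so that, without reflux, it cannot count.

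**Conclusion.** The point holds as a conflict between printed definitions. The stopping rule omits respiratory depression or apnoea without reflux, although the event's name includes respiratory depression and the article attributes the prior's 15% to both kinds. The respiratory endpoints behind feasibility omit apnoea and join two items that objective (iii) keeps apart. A promptly bagged apnoea counts there only if it raises pCO2 above 45 mmHg, or meets the bradypnoea rule and/or the saturation limit, depending on how the joined item is read.

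The size cannot be fixed from the article. At a combined rate of 30% the loss in prompt probability runs from 12.5 percentage points (50.4 − 37.9, 10% without reflux) through 24.0 (50.4 − 26.4, 20%) to 45.0 (50.4 − 5.4, 50%). These figures assume the stated rates and shares, a check after every child, and pooling of all 30. The documents do not support saying that apnoea goes unseen or that feasibility disregards it. The change should be made, because the rule as written does not count its own named event.

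**What to change.** - **Interim reviews:** keep the aspiration definition and give respiratory depression its own, without the reflux requirement; for example, apnoea or hypoventilation treated with bag and mask while on BCV. Ask the DMC to confirm that the 20% threshold still suits the wider event.
- **Safety endpoints:** list apnoea separately (any pause treated with bag and mask), and count bradypnoea and hypoxaemia separately, as objective (iii) does.
- **Secondary endpoints:** report the Trial treatments criterion directly: the number of hypoventilation or apnoea episodes, and in how many BCV supported breathing without bagging.
- Score children already enrolled from their records, and date the change as made after enrolment began.

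**Cost:** an amendment agreed with the DMC and, if not already collected, one case record form item (bag and mask given, time, reason). Treatment does not change. The rule will prompt more often, and some prompts will come from the disease itself. With the present prior and thresholds, the chance within 30 children is 5.4% at a combined rate of 15% and 14.4% at 20%. The Trial status section reports the trial as ongoing, so records for earlier children may be incomplete.

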### Safety endpoints

Aspiration (sudden decrease in oxygen saturations, and/or denovo presence of coarse chest crepitations, with evidence of gastric reflux/aspirate in the oropharynx).

Episodes of hypercarbia (defined as pCO2 level of greater than 45 mmHg).

Episodes of bradypnoea and hypoxaemia (oxygen saturation <92%) in a child with unrousable coma (Blantyre coma scale≤2) (bradypnoea defined as <10, 15 or 20 breaths/minute over 3 minutes for those aged <6m, 6–36m and >36m respectively).

Development of hypotension (defined as systolic blood pressure <50 mm Hg in children younger than 12 months; <60 mm Hg in children 1–5 years and <70 mm Hg in children olderthan 5 years of age). Use of additional ASMs. Neurological sequelae at day 180, Day 28 and day 180 mortality. Re-admission to hospital through day 180. Serious adverse events through day 180. Grade 3/4 adverse events through day 180. Length of initial hospitalisation. De-novo evidence of neurological impairments will be ascertained using a modified Kilifi Developmental Index
^
45
^ (which we have adapted to use for the COAST trial)
^
46
^.

Serious adverse events (SAEs) will use the standardized definitions. SAEs will be independently reviewed in real-time by the DMC. Adverse events will be graded following the Common Toxicity Criteria v5.0:

(
https://ctep.cancer.gov/protocoldevelopment/electronic_applications/docs/CTCAE_v5_Quick_Refe rence_5x7.pdf).

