**Methods:**

A Phase I trial conducted in Kilifi, Kenya designed to provide data on safety, feasibility and preliminary data on seizure control using prophylactic ASM (levetiracetam) and BCV as non-invasive ventilatory support in children with cerebral malaria. Children aged 3 months to 12-years hospitalised with
*P falciparum* malaria (positive rapid diagnostic test or a malaria slide), a Blantyre Coma Score ≤2 and a history of acute seizures in this illness are eligible for the trial. In a phased evaluation we will study i) BCV alone for respiratory support (n=10); ii) prophylactic LVT: 40mg/kg loading dose then 30mg/kg every 12 hours given via nasogastric tube for 72 hours (or until fully conscious) plus BCV support (n=10) and; iii) prophylactic LVT: 60mg/kg loading dose then 45mg/kg every 12 hours given via nasogastric tube for 72 hours (or until fully conscious) plus BCV support (n=10). Primary outcome measure: cumulative time with a clinically detected seizures or number of observed seizures over 36 hours. Secondary outcomes will be assessed by feasibility or ability to implement BCV, and recovery from coma within 36 hours. Safety endpoints include: aspiration during admission; death at 28 days and 180 days; and de-novo neurological impairments at 180 days.

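### The bradypnoea and hypoxaemia safety endpoint is narrower than objective (iii): it stops counting when coma ends although BCV continues, does not name apnoea, and leaves open whether both events must coincide

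*Protocol article*

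**What the plan says.** Four parts of the protocol article bear on this point.

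- **General objectives, specific objective (iii):** "To estimate the occurrence of adverse events using BCV, including episodes of bradypnoea or apnoea; hypoxaemia (oxygen saturations <92" per cent), followed by hypercarbia and aspiration. Bradypnoea or apnoea is one item and hypoxaemia another. No conscious level is attached to either.
- **Safety endpoints:** "Episodes of bradypnoea and hypoxaemia (oxygen saturation <92%) in a child with unrousable coma (Blantyre coma scale≤2"), with "bradypnoea defined as <10, 15 or 20 breaths/minute over 3 minutes for those aged <6m, 6–36m and >36m respectively". Apnoea does not appear. Aspiration, hypercarbia and hypotension in the same list carry no coma condition.
- **Trial treatments:** BCV runs from enrolment "until when a child can respond to stimuli (Blantyre coma scale 3 or more) sustained over a period of 4 hours". Feasibility there includes the ability "to support respiration during periods of hypoventilation or apnoea", and tolerability is "judged by children remaining comfortable during transition from coma to a semiconscious state".
- **Secondary endpoints:** feasibility is assessed partly by whether BCV averts the respiratory safety endpoints.

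**The concern.** Respiratory depression is the central safety question of this trial and the reason for using BCV. The endpoint differs from its objective in three ways: it adds a coma condition, it omits apnoea, and it joins with *and* two events that the objective lists separately. Each difference can only lower the count or leave it undefined.

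Two conclusions are exposed. One is the reported rate of respiratory events on BCV. The other is feasibility, because a device judged by whether it averts the respiratory safety endpoints looks better when fewer events qualify. The hours left out are also those of the transition out of coma, which is when the protocol judges tolerability. With 10 children per stage, a few uncounted events could change the description of a stage.

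**Working it through.** The plan states no figure for this endpoint, so there is nothing to reproduce. The check compares the texts and then finds the uncounted BCV time by subtraction.

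**1. Endpoint against objective**

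| Feature | Objective (iii) | Safety endpoint |
|---|---|---|
| Conscious level | no condition | Blantyre score 2 or less |
| Apnoea | named, as an alternative to bradypnoea | not named |
| Hypoxaemia | separate item | joined to bradypnoea by *and* |
| Setting | during BCV use | during coma |

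**2. BCV time outside the endpoint**

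Input from Trial treatments: BCV ends once a score of 3 or more has held for 4 hours. During those 4 hours the score is above 2 by definition, so the endpoint cannot count anything.

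Let c be the hours from enrolment to the end of coma. BCV time is then c + 4, and the uncounted share is 4/(c + 4). The protocol gives no distribution for c. I take 12 to 36 hours as an assumed range; its upper end is what the Statistical analysis section calls the maximum expected coma duration.

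- c = 12: 4/16 = 25%
- c = 24: 4/28 = 14%
- c = 36: 4/40 = 10%

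Four hours is a minimum. A child whose score rises to 3, falls back and rises again adds further uncounted time.

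**3. Apnoea during coma**

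Bradypnoea is a rate below an age threshold T over 3 minutes. I take T as printed and read the rule as an average over the 3 minutes. A child who otherwise breathes at k times T and pauses for a minutes qualifies when kT(3 − a)/3 < T, that is, when a > 3(1 − 1/k).

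- k = 1.5 (assumed): the pause must exceed 1 minute
- k = 2 (assumed): the pause must exceed 1.5 minutes

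Long apnoea in coma is therefore caught as bradypnoea, but a brief pause is not.

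**4. What else would capture the uncounted events**

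| Event after coma | Other specified capture |
|---|---|
| Severe respiratory event | SAE or grade 3/4 event, to day 180 |
| Carbon dioxide retention | hypercarbia endpoint, no coma condition |
| Aspiration | aspiration endpoint, no coma condition |
| Lesser bradypnoea, saturation below 92%, brief apnoea | none specified |

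The DMC monitoring event in Interim reviews does not fill the last row. It covers 72 hours without a coma condition and is labelled aspiration or respiratory depression. Its definition, however, asks for reflux or aspirate in the oropharynx.

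**The case against.** **The coma phrase may only describe the population.** Every child enters with a score of 2 or less, the general objective concerns cerebral malaria, and the Discussion calls BCV relevant only to children in coma. This reading is possible. But no other endpoint in the list carries the phrase, and BCV by rule continues after coma. A person coding events would have to take it as a condition.

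**Events are not lost.** A reader might infer that respiratory events late in treatment are missed altogether. The documents do not support that. SAEs and grade 3/4 events are collected whatever the conscious level, SAEs are reviewed by the DMC in real time, and hypercarbia, a marker of hypoventilation, is followed by capnography. This part of the objection stands. The gap is limited to lesser events that are not counted in this endpoint.

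**Apnoea is not wholly excluded, and *and* may simply join two event types.** Both points are fair. Long apnoea in coma qualifies as bradypnoea, and the wording does not prove that both events are required together. What remains is brief apnoea and an ambiguity that objective (iii) does not have.

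**Levetiracetam.** A reader might also infer that much of the levetiracetam course falls outside the endpoint, since the abstract has the drug given "for 72 hours (or until fully conscious"). This does not hold. Sample size determination, Trial treatments and Interim reviews all end dosing at coma resolution, in which case no scheduled dose follows coma. Objective (iii) concerns BCV only. The conflicting stopping statements must be reconciled, but that is a separate matter.

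**Conclusion.** The point holds as a mismatch between an endpoint and its objective. By definition, at least 4 hours of BCV per recovering child are not counted, or roughly 10% to 25% of BCV time for coma of 36 down to 12 hours. Brief apnoea is not named, and the joint or separate reading of the two events is unsettled.

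The 4 hours rest on the endpoint being applied literally and on BCV being worn until its stated end. The percentages rest on the assumed coma durations. The protocol gives no rate for lesser events after coma, so the number of events lost from the count cannot be estimated. No sample size, error rate or DMC stopping boundary is affected.

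**What to change.** In Safety endpoints, align the item with objective (iii):

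- delete the coma condition;
- list bradypnoea, apnoea and hypoxaemia as three separate endpoints, each counted at any conscious level from enrolment to the end of BCV;
- report each by Blantyre score (2 or less, 3 or more) as a descriptive split, which keeps the coma-only count available.

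Apnoea will need a working definition from the trial's clinicians; none is proposed here. Trial treatments allows the last 10 children to be treated with or without BCV. Objective (iii) does not cover a child without BCV, so a counting period for any such child would have to be stated separately.

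The cost is mainly wording. Clinical assessment already lists respiratory rate, oxygen saturation and conscious level among the bedside signs. The window should stop at the end of BCV: after 24 hours Table 1 schedules only bi-daily clinical assessments, which would not support close counting for a fixed longer period. The small downside is a higher reported event count, which the split by score makes interpretable.
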